#### 2.4.2 Study visits

After obtaining informed consent, participants will be given appointments for two study visits and one study visit for Part 1 and Part 2, respectively. The procedures are nearly the same for both study parts and are described below.

##### 2.4.2.1 Briefing

Every participant will be familiarized with the pain scale, the intradermal electrical stimulation model evoking pain, and the hyperalgesia and allodynia examinations. We have chosen not to provide a training session given its invasiveness, including the risk of habituation. Previous studies conducted by our research group using this model have also shown that this is not required (55, 64–67).

##### 2.4.2.2 Experimental setup

First, the study staff will place a venous catheter in the arm (opposite to the one used for electrical stimulation) of each participant.

Second, the intradermal electrical stimulation model to evoke pain will be installed. The model used in this study was first described by Koppert et al. (61) in 2001 and has since been used in numerous studies investigating pain, pain medications, hyperalgesia, and allodynia (55, 61, 64–70). The pain model used in the present study has been shown to provoke stable areas of secondary hyperalgesia to pinprick and touch caused by the activation of mechanoinsensitive C-nociceptors (71), a class of nociceptors shown to be activated electrically, preferentially at high current densities (72, 73).

In accord with the pain model, two microdialysis catheters with internal stainless-steel wires will be inserted in parallel (5 mm apart) into the intradermal, volar surface of the forearm (not used for venous access) for a length of approximately 10 mm (Figure 3). The catheters will be filled with 0.9% saline set to a continuous flow of 0.4 μl/min, ensured by a syringe pump, to facilitate conduction and to protect the tissue from eventual pH changes by the direct current. To ensure comparability of electrode nociceptor distance regarding subcutaneous tissue thickness after intracutaneous electrode placement only participants with a BMI between 18 and 25 were included. The stainless-steel wires will be attached to a constant current stimulator in combination with a pulse generator. This installation applies monophasic, rectangular electrical pulses 0.5 ms in duration with alternating polarity at a frequency of 2 Hz. The pulse generator pauses the stimulation for 30 s after conducting 500 pulses (approximately 4 min). The current will be increased to target a pain rating of 6 out of 10 on the NRS. Three further adjustments in current will be made every 5 min for the next 15 min to compensate for habituation. The final current will be kept constant until the end of the particular experiment. The total duration of electrical stimulation will be 200 min for Part 1; for Part 2, the duration of stimulation will depend on the results of Part 1. For sure, for ethical, technical and logistic reasons, there will be a limit to the observation time. This time limit will not substantially exceed the duration of stimulation that we know is safe for the skin, i.e., 200 min. At the end of the experiment, the current will be stopped, microdialysis catheters and venous access removed, thereby ending the study visit.

**FIGURE 3 F3:**
[figure not shown]
Experimental setup. **(A)** Intradermal electrical stimulation model evoking pain, first described by Koppert et al. (61). **(B)** Assessment of allodynia by using a dry cotton swab. **(C)** Assessment of hyperalgesia using a 256 mN von Frey filament.

##### 2.4.2.3 Timeline

Tables 1, 2 (for Part 1 and Part 2, respectively) give an overview over the timeline for each study visit.

**TABLE 1 T1:** Schedule for study procedures, part 1.

Possible OLP (intervention only)						x				
Questionnaires	x					x				x
NRS		x	x	x	x	x		x	every 5 min	x
Hyperalgesia		x		x		x		x	every 10 min	x
Allodynia		x		x		x		x	every 10 min	x
Electrical stimulation										
Time (min)	−5	0	5	10	15	20	25	30	…	200

NRS, numeric rating scale; OLP, open-label placebo.

**TABLE 2 T2:** Schedule for study procedures, part 2.

OLP / OLP Booster (Booster groups only)						x			x*	
Questionnaires	x					x			x*	x
NRS		x	x	x	x	x		x	every 5 min	x
Hyperalgesia		x		x		x		x	every 10 min	x
Allodynia		x		x		x		x	every 10 min	x
Electrical stimulation										
Time (min)	−5	0	5	10	15	20	25	30	…	**

*either on fixed time point (derived from Part 1; if data is inconclusive, at 100 min) or on-demand.

**measurement time period derived from Part 1. NRS, numeric rating scale; OLP, open-label placebo.

#### 2.4.3 Randomization

As every participant in Part 1 will receive all of the possible treatments, we are only able to randomize the order of the treatments, and thereby control for excitement and habituation effects.

For Part 2, group allocation will be randomized (control group, fixed-time “Booster” group, on-demand “Booster” group).

Randomization will be performed by study staff not involved in study assessments using a random number generator.^1^

#### 2.4.4 Blinding and other methods of minimizing bias

Due to the nature of an OLP study, it is not possible to blind participants. However, in Part 1 of our study, the assessor will be blinded to the intervention participants receive, and the study staff administering the intervention will not be involved in the assessments of the participant under their care.

Blinding of assessors will not be possible in Part 2 due to organizational reasons.

In order to ensure structural equivalence between the study groups and, where possible, blinding of the assessor, all groups will have the same number of visits by study staff giving the intervention. In Part 2, the intervention will be performed on participants by the assessor due to organizational reasons. The assessor will attempt to treat participants from all groups equivalently, although bias cannot be completely ruled out.

### 2.5 Intervention

#### 2.5.1 Experimental intervention

The experimental intervention will consist of two components, similar to our former study (32): a scripted, evidence-based treatment rationale and an OLP injection.

In Part 1, the intervention will be administered 20 min after start of the experiment. In Part 2, there will be two interventions: One 20 min after start of the experiment and one either at a fixed time point (derived from Part 1; or at 100 min if data are inconclusive) or on demand.

##### 2.5.1.1 Treatment rationale

Prior to the administration of the injection, a scripted evidence-based treatment rationale explaining placebo analgesia in pain in general and specifically in OLP will be provided. In the context of OLP treatments, this rationale is believed to be important in order to create a mental state of positive expectation (26), which in combination with the conditioning process elicited by the administration of an inert substance (54) will potentially lead to a placebo effect (i.e., decreased pain perception). A detailed explanation of placebo analgesia and the state of the literature on the effects of OLPs will be given in advance to participants in both groups as part of the written and oral IC procedure (Supplementary material).

The scripted treatment rationale will clearly state the fact that the placebo injections are inactive (inert) and contain only saline (i.e., a saltwater solution). Further, based on previous OLP studies (i.e., 45) it will contain the following discussion points, which have been tailored to refer to the context of the specific placebo analgesia treatment of this study (74):

1.Placebo effects of OLP can be **powerful** in some patients, especially in analgesia.2.**Treatment expectations** are found to be an important mechanism in placebo analgesia.3.In response to placebos, the body can **automatically** release **endogenous opioids,** which target the pain that patients experience in association with our experimental pain model.4.A **positive attitude** is helpful but is not absolutely necessary.

The exact wording of the scripted treatment rationale is available in the Supplementary material.

At the subsequent placebo application in Part 2, the patient will be reminded of the inertness of the injection and that OLPs might help to regulate pain (cf. Supplementary material).

##### 2.5.1.2 OLP injections

Syringes, 5 ml in volume, containing 5 ml of saline 0.9% will be administered intravenously as OLP via the venous access already established at the beginning of the study visit. The study staff administering the saline will ensure that the patient observes the injection.

#### 2.5.2 Control intervention

In Part 1 of the study, no treatment will serve as the control for comparison with the study intervention.

In Part 2, we aim to assess whether a repeated OLP dose is advantageous to a single dose. The control group in this part will receive only a single OLP injection and no repetition. The detailed procedure for the OLP administration is described above (cf. 2.4.1).

As control group participants are likely to experience disappointment (75), they will be reminded of the important role of control group participation after randomization (cf. Supplementary material for the exact wording). Moreover, study staff will strive to treat participants with equal empathy and warmth.

### 2.6 Outcome measures

A timeline of the assessments is shown in Tables 1, 2 for Part 1 and Part 2, respectively.

#### 2.6.1 Part 1

The primary endpoint of Part 1 is the area under the pain curve (AUPC) measured over 3 h according to an 11-point NRS following OLP administration. AUPC will be compared between the interventional visit (after receiving an OLP injection) *vs*. the control (non-interventional) visit.

Secondary endpoints of Part 1 are the differences between subjective pain ratings at each measurement point (NRS score every 5 min after OLP administration), the areas under the curve (AUCs) of area of hyperalgesia and area of allodynia, comparing the interventional *vs*. control (non- interventional) visit.

Hyperalgesia and allodynia will be measured immediately after pain ratings every 10 min as soon as an NRS of 6 is reached for the first time. Pinprick hyperalgesia will be assessed using a 256 mN von Frey filament and allodynia will be determined using a dry cotton swab. Measurements will be conducted from a more distant to a more central site along four orthogonal lines (distal, proximal, lateral, and medial) that will be drawn onto the skin with tick marks indicating each centimeter. Distal and proximal measurements will begin 12 cm from the site of electrical stimulation, and lateral and medial measurements 6 cm from the site. In both cases, the used measuring tool will be moved toward the site of stimulation in 1 cm increments until the subject reports either increased pain sensations from the von Frey filament (hyperalgesia) or an unpleasant “rougher” sensation from the cotton swab (allodynia). To create an area from these linear measurements, we are assuming that the areas are elliptical. The area is calculated using the formula $\frac{1}{4}\,\pi \times D\times d$ (D = proximal/distal diameter; d = medial/lateral diameter). For calculation reasons, we define 1 cm as the smallest value for the diameters.

#### 2.6.2 Part 2

The primary endpoint for Part 2 of our study is the AUPC (after OLP administration, as mentioned above) using the NRS during a time span derived from Part 1. We will compare the AUPCs of participants receiving a single OLP injection, participants additionally administered one repeated OLP injection at the time point derived in Part 1, and participants administered a second OLP injection on-demand.

Secondary endpoints of Part 2 are the same as those for Part 1 of the study.

#### 2.6.3 Other variables of interest

Other variables of interest are:

•Placebo attitudes & beliefs•Treatment expectations•Credibility of intervention•Safety outcomes

##### 2.6.3.1 Placebo attitudes & beliefs

Placebo attitudes and beliefs will be assessed before the setup of the pain model (for Part 1: only during the first visit) using two different scales:

•Placebo attitudes will be assessed using the second item of a questionnaire introduced by Fassler et al. (76), which assesses responders’ attitudes regarding non-specific therapies.•Participants’ belief in the power of placebos – a measure of the influence of patients’ pre-existing beliefs about placebos related to the effect of OLP – will be assessed using four-item questionnaire developed by Leibowitz et al. (24) and rated using a five-point Likert-scale. In line with the procedure proposed by Beaton et al. (77), we have translated the scale from English to German using back translation for verification.

##### 2.6.3.2 Treatment expectations

Treatment expectations will be assessed prior to the intervention (OLP alone and OLP & “Booster” for Parts 1 and 2, respectively) by the study staff administering the intervention. The assessment will be done using two items (“Expected Benefits,” “Desired Benefits”) of the Treatment Expectation Questionnaire developed by Alberts et al. (78) and translated into German (cf. Supplementary material).

##### 2.6.3.3 Credibility of intervention

If receiving an OLP injection, participants will be asked about the credibility of the OLP intervention at the end of the study visit (for details cf. Supplementary material).

#### 2.6.4 Safety outcomes

Due to the “inert” nature of placebos, no specific adverse events are expected. However, safety endpoints including the patient’s well-being, pain, skin irritation/infection, and allergic reactions/hypersensitivity will be noted. Thereby, we will assess adverse events of the pain model and/or the infusion of fluids through the venous access.

### 2.7 Data collection, management and storage

For data collection and management of participants’ responses at study visits, the secure web application REDCap (79) will be used as an electronic case report form. The system is hosted by the Center for Scientific Computing of the University of Basel (sciCore) and is password protected. Only authorized personal will be able to enter the system to view and/or edit data. Double data entry is performed in REDCap to digitalize all source documents, and all data entries are de-identified. Regular back-ups of study data take place, and back-ups are stored on secure webservers of the University Hospital Basel.

### 2.8 Sample size

For Part 1, we estimated how many participants are needed to achieve an 80% power to detect a difference of 45 in the AUPC between the interventional visit and the control visit. Based on data from our previous study (55), we assumed a standard deviation of 67 for the differences in the AUPC. The assumed difference and standard deviation of the difference correspond to a Cohen’s d of 0.7. Calculations were done assuming a two-sided alpha of 5% and using a two-sample *t*-test for comparison. The number of participants needed for Part 1 is 36.

The sample size for Part 2 was determined with respect to the comparison of the combined “Booster” (i.e., fixed-time and on-demand) groups *vs*. the control group. Including 105 participants allows to estimate a difference in the AUPC of 45 between the “Booster” groups and the control group and a difference of the AUPC of 51 between the fixed-time and on demand group with a power of 80%.We assume a standard deviation of 76 for the AUPC in all groups, which corresponds to a Cohen’s d of 0.6. Calculations were done assuming a two-sided alpha of 5% and using a two-sample *t*-test for comparison.

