### 2.3 Study population

We will include a total of 36 and 105 healthy adults in Part 1 and Part 2 of our study, respectively. Participants will need to meet all of the following inclusion criteria:

•Healthy volunteers (American Society of Anaesthesiologists Class I or II) aged 18–65 years•Body Mass Index between 18 and 25 kg/m^2^•Able to understand the study and the Numeric Rating Scale (NRS)•Able to give informed consent (IC)

The presence of any of the following exclusion criteria will lead to exclusion of the participant:

•Participation in a previous OLP study; for Part 2, this includes Part 1 of this study•Regular intake of medications or drugs potentially interfering with pain sensation (analgesics, opioids, antihistamines, calcium and potassium channel blockers, serotonin/noradrenaline reuptake inhibitors, and corticosteroids)•Neuropathy•Chronic pain•Neuromuscular disease•Dermatological disease (i.e., atopic dermatitis)•Psychiatric disorder•Pregnancy/lactation

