### 2.9 Statistical analysis

#### 2.9.1 Primary analyses

In Part 1, the effect of the OLP on the AUPC will be tested using a two-sample *t*-test. In order to account for additive period effects, the estimator of the treatment effect will be built as follows: The mean of the difference in the AUPC between the first and the second visit will be calculated for all patients who receive the placebo in the second visit. Then, the mean of the difference in the AUPC between the first and the second visit will be calculated for all patients who receive the placebo in the first visit. Then, the difference of the first and the second mean will be calculated and divided by two.

In Part 2, the AUPCs of the three groups will be compared as follows: First, the mean of the AUPC in the “Booster” groups (fixed-time and on-demand) will be compared to the mean of the AUPC in the control group using a two-sample *t*-test. If the test yields a significant difference, the mean of the AUPC in the fixed-time “Booster” group will be compared to the mean of the AUPC in the on-demand “Booster” group using a two-sample *t*-test.

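### Part 1 sample size: 36 is the per-group number for two independent groups; as a total under the planned cross-over analysis it gives about 97% power, not 80%

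*Protocol article*

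**What the plan says.** Section 2.8 (Sample size) sets the target for Part 1: "we estimated how many participants are needed to achieve an 80% power to detect a difference of 45 in the AUPC", comparing the interventional with the control visit. On variability it says "we assumed a standard deviation of 67 for the differences in the AUPC", and it repeats that definition in the next sentence: "The assumed difference and standard deviation of the difference correspond to a Cohen’s d of 0.7". The calculation uses a two-sided 5% level and a two-sample t-test, and ends with "The number of participants needed for Part 1 is 36".

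Section 2.3 confirms that this is a total: "We will include a total of 36 and 105 healthy adults in Part 1 and Part 2 of our study, respectively".

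Section 2.2.1 describes Part 1 as a confirmatory cross-over in which participants are their own controls and only the order is randomized. Section 2.9.1 gives the estimator. The mean first-minus-second-visit difference is taken in each sequence, and then: "Then, the difference of the first and the second mean will be calculated and divided by two".

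**The concern.** In a two-period cross-over, each participant contributes one within-person difference. The two sequences carry the treatment effect with opposite signs, so the contrast between their means estimates twice the effect, which is why section 2.9.1 halves it. A sample size for that test must set a contrast of 90, not 45, against the SD of 67. Section 2.8 appears instead to have entered 45 and 67 as though they described two independent groups, and then to have reported the per-group answer as the total.

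This is the only power statement for the part of the study that is called confirmatory. Anyone relying on it will take 45 as the difference Part 1 was built to detect, although the design can detect a clearly smaller one, and so will read a null result as less informative than it is. It is also the printed justification for the number of healthy volunteers who undergo two visits, each with 200 minutes of electrical stimulation.

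**Working it through.** **Inputs**

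- From section 2.8: difference 45, SD of within-person differences 67, two-sided alpha 0.05, power 80%.
- From section 2.3: 36 participants in total.
- From section 2.9.1: the estimator is half the difference between the two sequence means.
- Assumed: 18 participants per sequence, because the article states no allocation ratio.

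Power is computed from the noncentral t distribution.

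**1. Reproducing the stated 36**

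The standardised effect is d = 45/67 = 0.672 (rounded to 0.7 in the plan). A t-test between two independent groups needs n = 35.8 per group for 80% power. Power is 79.1% at 35 per group and 80.2% at 36 per group. The stated figure is therefore matched exactly as a per-group number, 72 in all. Using the rounded d = 0.7 gives 33.02, so 34 per group, which does not match.

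**2. Power of the planned analysis with 36 in total**

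- Expected contrast between sequences: 2 × 45 = 90.
- Standard error of the halved contrast: (67/2) × √(1/18 + 1/18) = 67/√36 = 11.2. Two independent groups of 18 would have 67 × √(2/18) = 22.3.
- Noncentrality: 45/11.17 = 4.03, with 36 − 2 = 34 degrees of freedom.
- Power: 97.5%. A simulation of 100,000 trials, with a period effect included, gave 97.4%.

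**3. Number needed for 80%**

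The same test with the same inputs needs 9.76 per sequence, so 10 per sequence or 20 in total (power 81.1%). A paired t-test needs 19.4, also 20.

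**4. What 36 participants can detect**

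- Difference detectable with 80% power: 32.2 (32.2/67 = 0.48 SD).
- Largest SD of differences that keeps 80% power at a difference of 45: 93.6.

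**5. Other ways to reach 36**

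| Calculation | Result |
|---|---|
| Sequence contrast taken as 45 (doubling omitted), 18 + 18 | power 49.9% |
| Same, 36 + 36 | power 80.2% |
| One-sided test, independent groups, d = 0.672 | 29 per group |
| Paired t-test on 36 differences | power 97.5% |

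With 67 defined as section 2.8 defines it, none of these gives 80% power with 36 participants in total.

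**6. Part 2 as a cross-check**

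The 105 for Part 2, read as a total with equal arms (70 against 35), gives 80.9% power for a difference of 45 with an SD of 76, as stated. The mismatch on this comparison is confined to Part 1.

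**The case against.** The strongest reply is that 67 may really be the SD of an AUPC at a single visit. A cross-over with 36 people yields 36 interventional and 36 control AUPCs. Treated as independent samples with SD 67, these give the stated 80% with 36 people in total, as a conservative calculation that ignores the pairing. Under the planned estimator that reading gives:

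| Assumed correlation between a person's two visits | SD of differences, 67 × √(2(1 − ρ)) | Power at N = 36 |
|---|---|---|
| 0 | 94.8 | 79.1% |
| 0.25 | 82.1 | 89.2% |
| 0.5 | 67.0 | 97.5% |

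So 80% is recovered only if a person's two visits are essentially uncorrelated. This does not rescue the text. Section 2.8 twice defines 67 as the SD of the difference, and uses a separate value, 76, for AUPCs in the Part 2 groups. If a single-visit SD was meant, the definition is wrong and still needs correcting. What does stand is that the per-group origin of 36 is an inference from exact reproduction; the article does not state it.

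A second reply is that sections 2.8 and 2.9.1 both name a two-sample t-test, and that halving the estimate leaves its p-value unchanged. That is true. The conflict lies in what is entered into the test, not in its name.

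A third is that the error is in the safe direction, so little follows from it. That bears on how serious the point is, not on whether the statement is correct.

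Finally, 67 comes from an earlier study with a 70-minute measurement period in healthy men, while Part 1 uses a 3-hour AUPC in a gender-balanced sample. The SD could be larger: at assumed values of 80 and 85, power for 45 is 91% and 87%. Any restated power should therefore be given conditionally on the SD.

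**Conclusion.** The point holds. On the plan's own inputs, 36 participants give 97.5% power for an AUPC difference of 45, against the stated 80%. About 20 would meet the stated target, so enrolment is roughly 16 above what the printed justification supports. At 80% power the detectable difference is about 32.

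This rests on 67 being the SD of within-person differences, as written, and on equal allocation to the two sequences. The estimator, the type I error rate and the validity of Part 1 are unaffected. What is wrong is the power statement.

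**What to change.** First confirm from the earlier data that 67 is the SD of within-person AUPC differences. If it is, keep 36 and replace the Part 1 power statement in section 2.8 with text along these lines:

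> For the estimator in section 2.9.1, and assuming an SD of 67 for the within-person differences in AUPC, 36 participants (18 per sequence) give about 97% power for a difference of 45 and 80% power for a difference of 32, at a two-sided 5% level. For a difference of 45, power stays at or above 80% for an SD of differences up to about 93.

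(The exact limit is 93.6; an SD of 94 gives 79.7%.) Add a sentence on why 36 is retained, for example as a margin against a larger SD or for precision in the time-course analysis that sets the booster time.

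If 67 turns out to be a single-visit SD, correct its definition, state the assumed correlation between visits, and recompute the power.

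Either route changes wording only. Enrolment and the analysis stay as they are.

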##### 2.1.2.2 Further objectives

In addition, we hypothesize that, in comparison to receiving a repeated OLP injection at a fixed time point, overall subjective pain ratings will be different when subjects receive the second application of OLP on-demand. Moreover, we hypothesize that there will be a difference in areas of hyperalgesia and allodynia when comparing subjects receiving a repeated OLP injection (i.e., two OLP injections) with subjects receiving only a single injection of OLP and when comparing subjects receiving the second application at a fixed time point with subjects receiving the second application on demand.

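### The 80% power stated for fixed-time versus on-demand is that of a stand-alone test; the planned sequence detects a difference of 51 in about 62% of trials at the planned effects

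*Protocol article*

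**What the plan says.** Section 2.8 sizes Part 2 on one contrast: "The sample size for Part 2 was determined with respect to the comparison of the combined" booster groups against control. It then gives two detectable differences for the same sample. The first is "Including 105 participants allows to estimate a difference in the AUPC of 45" for pooled boosters against control. The second is "a difference of the AUPC of 51 between the fixed-time and on demand group with a power of 80" per cent. The inputs are shared: "We assume a standard deviation of 76 for the AUPC in all groups", "Calculations were done assuming a two-sided alpha of 5" per cent, and a two-sample t-test.

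Section 2.9.1 sets an order. Pooled boosters are tested against control first. Then: "If the test yields a significant difference, the mean of the AUPC in the fixed-time" booster group is compared with the mean in the on-demand group. Section 2.8 does not mention this condition.

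The second comparison answers a hypothesis of its own in section 2.1.2.2, that "overall subjective pain ratings will be different when subjects receive the second application of OLP on-demand" rather than at a fixed time.

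**The concern.** The two sections do not fit together. A reader of section 2.8 takes 80% as the chance that the planned analysis finds a 51-point difference between the two booster timings. Under section 2.9.1 that finding needs two significant results, so the chance cannot exceed the power of the first test and will usually be lower.

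The size of the loss depends on the pooled effect, for which section 2.8 makes no allowance in the second figure. If the benefit sits mainly in one booster arm, pooling dilutes it and the first test becomes the bottleneck. What is at stake is how a missing or non-significant timing comparison is read: as a question tested with 80% power, or as one the sequence may not have reached. Section 2.9.2 applies the same analysis to the hyperalgesia and allodynia AUCs, so the condition carries over to them.

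**Working it through.** **Inputs.** From section 2.8: N = 105, SD 76 in every group, differences 45 (pooled boosters vs control) and 51 (fixed-time vs on-demand), two-sided 5%, two-sample t-tests. From section 2.9.1: the second test only after a significant first. Allocation is not given (section 2.4.3 says only "For Part 2, group allocation will be randomized (control group, fixed-time" and on-demand groups). I assume 35 per arm, which reproduces both stated powers.

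**Step 1: reproduce the stated figures, each test alone.** The noncentrality is difference / (SD × √(1/n₁ + 1/n₂)).

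- Pooled vs control, 70 vs 35: 45 / (76 × 0.2070) = 2.86. Power is 81.6% (normal approximation) or 80.9% (noncentral t).
- Fixed-time vs on-demand, 35 vs 35: 51 / (76 × 0.2390) = 2.81. Power is 80.2% (normal) or 79.0% (noncentral t).

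Both agree with the stated 80%. The second is the power of an unconditional 35 vs 35 test.

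**Step 2: the sequence.** The two contrasts are orthogonal, so the chance that both tests are significant is close to the product: 0.81 × 0.79 = 0.64.

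One adjustment lowers this slightly. If the booster arms are 51 apart, each lies 25.5 from their common mean, and this enters the error SD of the first t-test: √(76² + 70 × 25.5² / 103) = √(5776 + 442) ≈ 78.9. The noncentrality of the first test falls from 2.86 to about 2.76, and its power from 80.9% to about 79%.

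**Step 3: simulation of the two-step rule** (400,000 trials per scenario, 35 per arm, SD 76, pooled-variance t-tests). Effects are AUPC reductions against a single injection.

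| Booster effects | Mean | Difference | First test | Second test alone | Both |
|---|---|---|---|---|---|
| 70.5 and 19.5 | 45 | 51 | 78.9% | 79.1% | 62.2% |
| 51 and 0 | 25.5 | 51 | 33.5% | 79.0% | 26.2% |
| 85.5 and 34.5 | 60 | 51 | 95.9% | 79.1% | 75.8% |
| 96 and 45 | 70.5 | 51 | 99.2% | 79.1% | 78.5% |
| 70.5 and 0 | 35.25 | 70.5 | 54.8% | 96.9% | 53.0% |

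The first row has both planning differences true at once: 45 + 25.5 = 70.5 and 45 − 25.5 = 19.5. With Welch tests the joint figures in the first two rows are 62.7% and 27.4%.

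**Step 4: conditional power.** In the first row, 62.15 / 78.88 = 78.8%. Once the first test is significant, the second keeps its stand-alone power. The 80% is therefore acceptable as a conditional figure, but not as the power of the sequence.

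**The case against.** The best defence is that nothing has been miscalculated. Section 2.8 gives a figure per comparison, it reproduces, and it is right conditional on the first test. The sample size was set on the pooled comparison, and 51 is what that sample then allows for a further objective in a proof-of-concept part. Fixed-sequence testing is a legitimate way to control multiplicity, and lower joint power is its known price. All of this stands, and it limits the importance of the point. It does not remove the mismatch: section 2.8 attaches no condition to the figure, and section 2.9.1 lists the conditional test under primary analyses.

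Three stronger readings are tempting and not supported.

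- *That 62% is the true power.* It belongs to one scenario, with booster effects of 70.5 and 19.5, which the protocol never states. With the arms 51 apart, the joint figure runs from 26% to about 78% over the cases tabulated.
- *That the sequence will most likely hide a real timing difference, or usually stops at the first test when only one booster works.* At the planned effects it succeeds in 62% of trials. With effects of 70.5 and 0, the first test is significant in 55% of trials and both tests in 53%. Larger losses arise if one booster worsens pain relative to a single injection, but the protocol gives no reason to expect that.
- *That the estimate will be withheld if the first test fails.* The article does not say so, and reporting details may sit in the full protocol or SAP.

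**Conclusion.** The concern holds in a limited form. The 80% in section 2.8 for fixed-time versus on-demand describes a stand-alone test, whereas section 2.9.1 makes that test conditional. The planned procedure detects a difference of 51 with probability of about 62% if the mean booster effect is 45, and about 26% if the effects are 51 and 0. It approaches 79% only when the mean effect is well above the planned 45.

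These figures rest on 35 per arm (assumed), SD 76 in every arm, two-sided 5% tests and normally distributed AUPC. The sample size is not in question, and the pooled comparison keeps roughly 81% power when the booster arms do not differ. The fault is in a stated figure, not in the design.

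**What to change.** 1. In section 2.8, label the 80% for the difference of 51 as conditional on a significant pooled test. Add the sequential power with its scenario: about 62% if the mean booster effect is 45 and the booster arms differ by 51, with 35 per arm. Giving the 51-and-0 case (about 26%) beside it would show the dependence on the pooled effect.
2. In section 2.9.1, state that the fixed-time versus on-demand difference will be reported with its 95% confidence interval whatever the first test shows, and keep the condition only for a confirmatory claim.
3. Optionally, run the first test as the contrast (1/2, 1/2, −1) in a three-arm linear model, so that a difference between booster arms does not inflate the error SD. At the planned effects this gains about 2 points: first test 79.0% to 81.1%, both tests 62.3% to 64.3%, in a separate simulation of 200,000 trials.

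Items 1 and 2 cost only wording and a less favourable stated figure. Item 3 changes the prespecified test, so it should be fixed before Part 2 data are analysed. None of them changes the sample size or the conduct of the trial.
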